### Preliminary Work on Remote Delivery of Cognitive Health Interventions

Our preliminary work investigated the remote delivery of action-based cognitive remediation (ABCR) and MCT [26]. ABCR is a distinct form of CR, which integrates the traditional cognitive training techniques of CR with simulated workplace scenarios and goal setting [27]. This work involved evaluating 3 crucial early implementation outcomes: acceptability, appropriateness, and feasibility for both patients and therapists. Across 6 cohorts (3 ABCR and 3 MCT) conducted within Montreal, patients expressed high acceptability, with overall satisfaction for expectations and perception of progress. The interventions demonstrated feasibility; 36 participants completed therapy, attending an average of 10 MCT sessions and 12 ABCR sessions.

Using recently developed measures [28], therapists also reported excellent acceptability, appropriateness, and feasibility of the interventions [26]. Several facilitators and barriers to delivering these digital interventions were also identified. Barriers comprised patients’ clinical status (eg, more severe symptomatology and medication side effects), interaction issues (eg, lack of involvement and decreased accountability), technological challenges (eg, access to devices and the internet), program elements (eg, language options), and scheduling conflicts. On the other hand, facilitators included patients’ motivation to learn, therapist characteristics (eg, warmth and proper training), financial support for internet connectivity, program support (eg, education on interventions and ice breakers), and logistical adjustments (eg, offering evening sessions and forming smaller groups).

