### Statistical Analysis

#### Power

Monte Carlo simulations computed in R (R Foundation for Statistical Computing) were used to estimate the required sample size for our proposed models. Our analyses, based on simulated data, suggest that a total sample size of 300 provides enough statistical power (up to 90%) to detect anticipated effect sizes on primary outcomes of cognitive capacity and cognitive bias based on values from our group and those reported in the literature (CR: *d*=0.50 and MCT: *g*=0.27) [9,20,27,31]. The attrition rate for our digital groups has been approximately 20%; we will nonetheless conservatively adjust for an attrition rate of 30%. When considering the propensity score, this results in a requirement of 390 participants. Comparable studies using the same interventions and statistical methods in in-person settings have included similar sample sizes as those proposed at our individual sites [68,69]. Further, this sample size will allow us to detect anticipated effect sizes on secondary outcomes related to symptomatology (CR: *d*=0.28 and MCT: *g*=0.38) [70,71] and functioning (CR: *d*=0.36-0.51 and MCT: *d*=0.37) [31,71,72]. We also anticipate that the proposed sample size will be adequate to explore sex- and gender-related differences using subgroup analyses of 2 (male and female) and 4 (men, women, nonbinary, and other) groups, respectively.

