#### Data Analysis

Data related to the analysis of objective 1, focusing on clinical effectiveness, will be compared between both interventions. Primary and secondary outcomes will be compared between the 2 interventions, using one as the active control for the other. First, propensity score matching will be used to identify a subset of participants who will comprise the active control group that is equivalent to the intervention group on background variables (sociodemographic variables, illness duration, medication dosage, length and nature of prior treatment as well as subjective reports of cognitive capacity and cognitive biases). Then, Z-standardized outcome data will be compared between the groups with generalized linear mixed effect modeling techniques using R software. Factors of interest will include fixed time (pre, post, and follow-up), fixed treatment (ABCR and MCT), fixed time and treatment interaction (time*treatment), random site (CIUSSS de l’Ouest-de l’Ile de Montréal, the Royal’s Institute in Ottawa, Kingston Health Sciences Centre, Ontario Shores Centre for Mental Health Sciences in Toronto, and Vancouver Coastal Health), random intercepts (participants’ ID), and random slopes (participant*time). Age, illness duration, medication dosage, length, and nature of prior psychological treatment will also be included as fixed covariates. This procedure will be done twice, with the active control group subset using propensity score matching. This approach ensures that participants are not counted twice and is an integral part of the propensity score matching procedure. Statistically, performing the procedure twice helps to validate the robustness of the matching process without introducing bias, as each participant is only included once in each comparison. Specifically, the procedure will be as follows: (1) ABCR as the intervention and MCT as the active control and (2) MCT as the intervention and ABCR as the active control. Missing data pattern will be assessed for whether it is missing completely at random, missing at random, or not at random [73]. If data are missing at random, multiple imputation will be applied [74]; if data are missing not at random, then the robustness of the primary analyses will be evaluated through sensitivity analyses.

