## Results

A pilot pragmatic trial [26] has been conducted previously at the Montreal site, where 6 cohorts (3 ABCR and 3 MCT) were run, evaluating 3 early implementation outcomes: acceptability, feasibility, and engagement. Of the 28 participants attending at least 1 session, 21 completed more than half of the sessions. All completers reported a positive experience with therapy, 2 of 3 were not bothered by the remote setting, and 16 trusted the confidentiality of the information shared. Technology did not appear to significantly impede program participation. Therapist-rated levels of engagement were also satisfactory [26].

This study was approved by the institutional review board by September 2023. From September 2022 to January 2023 staff training was conducted across all 5 sites. Intervention materials including intervention manuals and digital portals began in June 2022 and continued until November 2023. Therapist training began on the E-Cog learning platform in April 2023 and is ongoing. All sites began recruitment in 2023 and have run cohorts of MCT and ABCR in their respective regions. Quantitative data collection occurs prior to and following the intervention group and is ongoing, qualitative data collection for implementation assessment began in summer 2024 and is ongoing. As of winter 2024, a total of 114 participants have been recruited and 32 therapists are enrolled in the E-Cog training platform with 25 therapists having completed the training. The updated project timeline can be accessed for those who create free accounts on the iCogCA Hub web page [77].

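### The sensitivity analysis for missing data is run only on a finding of MNAR, which observed data cannot separate from MAR; it should be run unconditionally

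*Protocol article*

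**What the plan says.** The Data Analysis section of the protocol article sets a rule in three parts.

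- Classification: "Missing data pattern will be assessed for whether it is missing completely at random, missing at random, or not at random".
- Action under MAR: "If data are missing at random, multiple imputation will be applied".
- Action under MNAR: "if data are missing not at random, then the robustness of the primary analyses will be evaluated through sensitivity analyses".

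No other section states a sensitivity analysis for missing data, so the MNAR branch is the only route to one.

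The same section fixes the primary model without any condition on missingness. It is a mixed-effects model on standardized outcomes at pre, post and follow-up, with treatment, time, their interaction, site, participant-level random effects and named covariates.

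On the amount of loss, the Power section reports "The attrition rate for our digital groups has been approximately 20" percent and adds that "we will nonetheless conservatively adjust for an attrition rate of 30" percent. The first figure is experience and the second is a planning allowance.

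**The concern.** MAR and MNAR differ only in how missingness relates to values that were not recorded. A rule that needs the analyst to find out which one holds asks the data a question they cannot answer. Two things can then happen. MAR is assumed, the imputation is done, and no check follows, although an analysis that rests on MAR is exactly the one that needs checking. Or someone decides, with the data in hand, that MNAR is likely and adds sensitivity analyses at that point.

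At stake is whether readers can tell how far the ABCR versus MCT contrast depends on an untestable assumption, in a trial where a fifth or more of the outcome data may be absent. This is a fault in the stated rule, not a detail deferred to a SAP. A SAP that followed the rule would inherit the fault, and one that corrected it would depart from the published text.

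**Working it through.** **1. The plan's own attrition figure.** The Power section goes from 300 to 390 participants with a 30% allowance. 300 × (1 + 0.30) = 390 reproduces the target; 300 / (1 − 0.30) = 429 does not. The arithmetic is thus consistent with 30% as the planning figure. Of 390 recruited, 30% loss is 117 (273 remain) and 20% loss is 78 (312 remain). Whether 390 is a large enough inflation is a separate matter.

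**2. Why the branch cannot be decided from the data.** Let R record which outcomes are observed. The full-data distribution factors as

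f(y_obs, y_mis, R) = f(y_obs, R) × f(y_mis | y_obs, R).

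The data inform only the first factor. For any MNAR model, keep the first factor and replace the second with one that meets MAR. The new model fits the observed data equally well. A comparison of recorded characteristics between people with and without missing scores can count against MCAR; it cannot go further.

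**3. What MAR imputation can leave behind.** A simulation used assumed settings: 400,000 cases, a pre-post correlation of 0.6, and the log-odds of dropout equal to −0.95 − 0.8 × (unseen post score). The results were:

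- missing: 30.2%
- true post mean: 0.00 SD
- mean of observed cases: 0.21 SD
- mean after regression imputation from the pre score: 0.14 SD

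Imputation removed about a third of the error: (0.21 − 0.14) / 0.21 = 0.33. The remaining 0.14 SD is for one group's mean. It reaches the contrast only as far as informative dropout differs between arms.

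**4. Size in the contrast.** Let m be the missing fraction and δ the amount, in SD, by which missing scores in one arm depart from the MAR prediction beyond any such departure in the other arm. With equal m in both arms, shift = m × δ. The documents give no δ; 0.3 to 0.5 SD is an assumption. The yardsticks are the anticipated effects in the Power section, g=0.27 for MCT and d=0.50 for CR.

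| m | δ | Shift (SD) | Share of 0.27 | Share of 0.50 |
|---|---|---|---|---|
| 0.20 | 0.3 | 0.06 | 22% | 12% |
| 0.20 | 0.5 | 0.10 | 37% | 20% |
| 0.30 | 0.3 | 0.09 | 33% | 18% |
| 0.30 | 0.5 | 0.15 | 56% | 30% |

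**5. Tipping values.** The δ that removes the whole effect is effect / m. At 30% missing this is 0.27/0.30 = 0.90 SD and 0.50/0.30 = 1.67 SD. At 20% it is 0.27/0.20 = 1.35 SD and 0.50/0.20 = 2.50 SD. Erasing an effect entirely would need a large departure; weakening the smaller one materially would not.

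**The case against.** The strongest reply is that the main analysis is not left open. The mixed model is fixed in advance, and if it is fitted by likelihood to all available visits it is already valid under MAR. The sensitivity analyses are described as testing that analysis, not replacing it. This stands. A reader might infer that the primary method will be picked after looking at the data; the text does not support that.

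Next, assessing the pattern need not mean a statistical test. Under Cognitive Health Interventions, staff contact participants who miss several sessions in a row and discuss barriers. Such reasons are a fair basis for suspecting MNAR, so it goes too far to say that the check would never be triggered. They still cannot establish MNAR, and the decision remains one of judgement. Nor does the wording forbid sensitivity analyses under MAR; it simply does not commit to any.

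A reader might also take the pilot as evidence of informative dropout, since its barriers include "more severe symptomatology and medication side effects". Those are barriers to delivering the interventions, listed beside scheduling, language and device access. They are not recorded reasons for missing outcomes. Missing a session is not missing an assessment: assessments are paid for, and primary-outcome collection is to be prioritized. The pilot statement "Of the 28 participants attending at least 1 session, 21 completed more than half of the sessions" likewise concerns sessions. Symptoms are measured at baseline, so dropout explained by baseline severity could be MAR if the analysis conditions on it, although the covariates named for the model include no symptom score.

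Finally, the illustration sets the departure in one arm, or as a difference between arms. The document does not show differential dropout. It is possible, since the programs differ in length (16 sessions over 8 weeks against 12 over 6) and participants help choose between them, but that does not demonstrate it.

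**Conclusion.** The concern holds as a fault in the rule. The only stated robustness check for missing data depends on a classification that observed data cannot deliver, so it may be omitted where MAR is assumed or added by judgement after the data are seen. Choice of the imputation step is conditional in the same way; the primary model is not.

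With an assumed between-arm difference of 0.3 to 0.5 SD in departure from MAR, the contrast moves by 0.06 to 0.10 SD at the 20% attrition seen so far and by 0.09 to 0.15 SD at the 30% allowed for. A reader might fasten on the largest share, 56% of g=0.27. It requires the 30% allowance, the upper δ and the smaller effect all at once, so it is the top of an illustrative range and not an estimate of bias. If informative dropout is similar in the two arms, the shift is smaller.

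**What to change.** Delete the MAR/MNAR branch from the Data Analysis section and put two statements in its place.

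1. The primary analysis takes MAR as its working assumption, either through the likelihood mixed model on all available visits or through multiple imputation, and the text says which.
2. A prespecified MNAR sensitivity analysis, for example delta-adjusted imputation or a tipping-point analysis with δ allowed to differ by arm, is always run on the primary outcomes, whatever the missingness assessment suggests.

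Describing missingness patterns and reasons remains useful for interpretation, but should not decide which analyses are done. The auxiliary variables and the range of δ can be left to the SAP.

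The cost is about two sentences and one more scripted analysis, with no new data collection. The article describes recruitment and data collection as ongoing, so the change could be made before the final analysis.

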## Results

A pilot pragmatic trial [26] has been conducted previously at the Montreal site, where 6 cohorts (3 ABCR and 3 MCT) were run, evaluating 3 early implementation outcomes: acceptability, feasibility, and engagement. Of the 28 participants attending at least 1 session, 21 completed more than half of the sessions. All completers reported a positive experience with therapy, 2 of 3 were not bothered by the remote setting, and 16 trusted the confidentiality of the information shared. Technology did not appear to significantly impede program participation. Therapist-rated levels of engagement were also satisfactory [26].

This study was approved by the institutional review board by September 2023. From September 2022 to January 2023 staff training was conducted across all 5 sites. Intervention materials including intervention manuals and digital portals began in June 2022 and continued until November 2023. Therapist training began on the E-Cog learning platform in April 2023 and is ongoing. All sites began recruitment in 2023 and have run cohorts of MCT and ABCR in their respective regions. Quantitative data collection occurs prior to and following the intervention group and is ongoing, qualitative data collection for implementation assessment began in summer 2024 and is ongoing. As of winter 2024, a total of 114 participants have been recruited and 32 therapists are enrolled in the E-Cog training platform with 25 therapists having completed the training. The updated project timeline can be accessed for those who create free accounts on the iCogCA Hub web page [77].

## Discussion

### Overview

This study aims to address the crucial clinical needs of individuals with SSD by evaluating the feasibility and effectiveness of delivering cognitive health interventions through a digital platform. We hypothesize that these interventions will yield positive outcomes in terms of accessibility, engagement, symptom reduction, and cognitive functioning.

### Principal Findings and Comparison to Prior Work

The objectives of this study are 2-fold, focusing on both service users and mental health care providers. The first objective aims to assess the effectiveness of digital cognitive health interventions in enhancing accessibility and engagement for individuals with SSD. If proven effective, these interventions may provide an evidence-based framework for other service providers providing care for individuals with psychotic disorders and could be adapted for other populations receiving mental health services where these interventions show similar efficacy (eg, mood disorders) [78,79]. Objective 2 aims to identify facilitators and barriers to digital delivery and a digital training platform for clinicians. We anticipate that this study will introduce and validate our platform to train and supervise mental health care practitioners to deliver these interventions, which will then be made accessible to the broader mental health community. Further, these findings will furnish crucial information for the implementation of digital health technologies to improve access to psychosocial therapies for optimized care. These findings will be used to guide the implementation of similar projects across Canada. Notably, New York State has already fully integrated CR into its psychiatric care systems [80], and parallel efforts are underway in Australia [81] and the United Kingdom [82]. Collaborating with a National Steering and Implementation Committee, we will test our set of tools based on the CFIR and make them accessible to the mental health community. Site-specific implementation committees, which include patient partners, will assist with the local implementation of our cognitive health interventions.

### Strengths and Limitations

This proposed national collaborative effort serves as a catalyst for leveraging digital technology to enhance the adoption of evidence-based psychosocial interventions. This study has several strengths. The first is the implementation across multiple Canadian sites, which enhances the generalizability of our findings. Second, we also aim to engage a broad pool of participants, both service users and mental health practitioners, by using digital technology to provide the intervention and training. Encouragingly, previous studies have demonstrated that a significant portion of those with severe mental illnesses appear to have the required technological access and ability to join, participate, and benefit from digital services [83,84]. We have also a planned comprehensive collection of quantitative and qualitative data. Our data collection plan involves service users and mental health practitioners at multiple time points, allowing us to answer our research questions in a multifaceted manner. Finally, we have engaged with diverse stakeholders throughout various stages of the study, including those with lived experiences, clinicians, researchers, and managers.

Some limitations of our study include the nonrandomized concurrent controlled design, which raises concerns about potential group differences. However, we will address this by statistically controlling for measurable background characteristics. Second, although we aim to engage a broader population by providing services using a digital format, we acknowledge that there could be variability to technology access. We have planned to provide tablets and internet to service users without access to technology. For service users or health care providers unfamiliar with technology, we will also offer orientation sessions to help them become comfortable with the digital format. Next, the recruitment of therapists within a research setting may not reflect therapists involved in nonresearch settings. In addition, although we have taken great care in selecting instruments that have been validated in our population and available in both English and French, some limitations may still exist with the instruments chosen. For instance, ceiling effects have been observed in the Cambridge Neuropsychological Test Automated Battery cognitive test. Finally, there may exist differences across 5 sites in training experiences and implementation fidelity. We plan to attend to this by standardizing training and fidelity checks conducted across all sites.

### Conclusions

In summary, this project aims to address pressing clinical needs related to cognitive impairments and biases in SSDs. By leveraging digital technologies, it aims to facilitate the adoption of evidence-based interventions within clinical settings, support future implementation of similar initiatives, and validate an adaptable platform designed for widespread use.

## Appendix

Multimedia Appendix 1 Example of iCogCA recruitment pamphlet.

Multimedia Appendix 2 E-Cog training platform home page.

Multimedia Appendix 3 E-Cog training platform action-based cognitive remediation introduction page.

Multimedia Appendix 4 E-Cog training platform metacognitive training introduction page.

## Abbreviations

ABCR: action-based cognitive remediation
CFIR: Consolidated Framework for Implementation Research
CIUSSS: Centre intégré universitaire de santé et de services sociaux
CR: cognitive remediation
MCT: metacognitive training
REB: research ethics board
SSD: schizophrenia spectrum disorder
